### Sample size

Sample size calculations were performed for the primary outcome: SPPB. On the basis of acute care in-patient populations and using the MID between the treated group of 2 points of a total possible score of 12 points, with an SD of 2.7 points [36], it is anticipated that 29 participants are required per group (58 in total), based on a two-sample *t* test. This was based on a type I error rate of 0.05, which is consistent with recommendations and a power of 0.80 [61]. This sample was increased to 72 participants on the basis of a predicted 20% dropout rate, based on our previous study in the same population conducted at both participating hospitals [17].

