### Statistical methods

Statistical analyses will be performed by the biostatistician. All data will be analysed using the intention-to-treat principle. Descriptive statistics, including mean and SD, median and interquartile range, number and percent, and frequency will be used to summarise data (depending on distribution and type of data). This also includes participant demographics and adherence to sternal precautions. A comparison between the two hospitals will be conducted on the demographic profile of the participants to establish differences in each presenting population.

The primary outcome—the change from baseline to 4 weeks in the SPPB—will be analysed using a mixed between-and-within subjects analysis of variance with repeated measures across participants. The primary hypothesis will be examined by a contrast evaluating change from baseline to the 4-week time point in the modified sternal precaution group compared with the standard care group. The analysis will be carried out according to the intention-to-treat principle, based on the groups to which participants were randomised. The interactions between group and time will be examined first to assess the effect of intervention, and, if no interaction is present, then group and time main effects will be examined. If there are issues with non-normality or ceiling/floor effects of the SPPB, transformation or dichotomisation will be considered. If there are participants who are not following the assigned group protocol, we will consider a supplementary per-protocol analysis. Key secondary outcome data (including upper limb function, pain, kinesiophobia and HRQoL) will be summarised and analysed similarly to the primary outcome.

Logistic regression will be used to determine pre-, peri- and post-operative risk factors associated with the development of post-sternotomy complications. This will be an exploratory analysis which may identify trends of predictors reported in the literature having an individual effect on post-operative sternal complications (i.e., female sex, diabetes mellitus, obesity, bilateral internal mammary artery grafts, re-operation for post-operative complications, and blood product requirement were reported as significant predictors of sternal infection). For all tests conducted, a *p* value <0.05 (two-tailed) will be considered statistically significant, and mean differences (95% confidence intervals) will be reported.

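### The fallback from a null group-by-time interaction to the group main effect should be removed or labelled descriptive, because that main effect includes the pre-randomisation baseline and has no stated role in deciding the primary hypothesis

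*Protocol article*

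**What the plan says.** All of this is in the Protocol article.

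- **Named primary test (Statistical methods).** The primary outcome is SPPB change from baseline to 4 weeks, analysed by a mixed between-and-within-subjects ANOVA. "The primary hypothesis will be examined by a contrast evaluating change from baseline to the 4-week time point", modified precautions against standard care.
- **Sequence (same paragraph).** Group-by-time interactions are examined first, as the way to judge the intervention. Then, "if no interaction is present, then group and time main effects will be examined".
- **Significance level (end of the section).** Two-tailed p<0.05 applies to all tests, with no division between them.
- **Timing (Randomisation and allocation).** The envelope is opened only after baseline testing, so the baseline SPPB precedes randomisation.
- **Secondary outcomes (Statistical methods).** Upper limb function, pain, kinesiophobia and quality of life are to be analysed in a similar way, so the sequence carries over to them.
- **Planning values (Sample size).** A difference of 2 points "with an SD of 2.7 points", type I error 0.05 and "a power of 0.80".

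**The concern.** When randomisation follows baseline, a treatment effect shows up as a difference between groups in change, which is the group-by-time interaction. An absent interaction is therefore the negative result. Going on to the group main effect gives the comparison a second look with its own full 0.05.

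The main effect is also the wrong quantity. It averages each group's scores over all visits in the model, including one that the intervention cannot have influenced. It understates a real effect and takes in any chance difference present at baseline.

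At stake is what may be reported as an effect of modified precautions if the 4-week contrast is null. The paragraph names the deciding contrast but does not say what a significant group main effect would mean.

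**Working it through.** **Inputs.** From Sample size: difference 2, SD 2.7, two-sided alpha 0.05, power 0.80, 29 per group. The article gives no within-person correlation for planning. I assume 0.3 to 0.78; the upper value is the 6-month average ICC cited for the SPPB under the primary outcome. It does not state how many visits enter the primary model, so two (baseline, 4 weeks) and three (adding 3 months) are both shown.

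**1. The plan's own figure.** n per group = 2 × [(1.960 + 0.842) × 2.7 / 2]² = 28.6, so 29, as stated: "29 participants are required per group (58 in total), based on a two-sample" t test. Allowing for 20% dropout, 58 / 0.8 = 72.5, against the stated 72. The sample size is not in question here.

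**2. Dilution.** Take a true difference of 0 at baseline and 2 points at every later visit. The group main effect estimates the average over visits:
- two visits: (0 + 2) / 2 = 1.0 point;
- three visits: (0 + 2 + 2) / 3 = 1.33 points.

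**3. Carry-over of chance imbalance.** With 29 per group the standard error of the baseline difference is 2.7 × √(2/29) = 0.71, so a 1-point gap is not unusual. With no treatment effect, equal variances and common correlation ρ, a baseline gap d over T visits gives an expected main-effect estimate of d × [1 + (T − 1)ρ] / T. For d = 1:

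| Visits | ρ = 0.5 | ρ = 0.78 |
|---|---|---|
| 2 | 0.75 | 0.89 |
| 3 | 0.67 | 0.85 |

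**4. Error rate if either result counts.** With equal variances and a common correlation, change from baseline and the person's mean over visits are uncorrelated. For two visits, Cov(Y1 − Y0, Y1 + Y0) = Var(Y1) − Var(Y0) = 0. Under normality the two tests are then independent, and with no effect

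P(interaction significant, or not significant but main effect significant) = 0.05 + 0.95 × 0.05 = 0.0975.

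Simulation with 29 per group, SD 2.7, ρ from 0.3 to 0.78, two or three visits, and the interaction taken as the 4-week contrast or as an omnibus test, gave about 0.095 to 0.106. The assumed correlation hardly matters.

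**5. Error rate if only the named contrast counts.** There is one test at 0.05, so the error is 0.05; the simulations agree (0.049 to 0.051).

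**The case against.** The strongest reply is that the primary test is already single and named. The Abstract, the trial objective and the Statistical methods all point to 4 weeks, and the purpose clause about judging the intervention attaches to the interaction. The main effects are only to be examined, which is ordinary ANOVA reporting, and a main effect cannot confirm a hypothesis about change. This largely stands. A reader might infer that the plan as written doubles its primary error rate. The document does not support that, because it nowhere makes a significant main effect a success. What remains is that it does not exclude that use either, and it places the step directly after the assessment of the intervention effect, at an undivided 0.05.

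It is also fair that the main-effect test on its own keeps its size. Over repeated randomisations, chance imbalance adds noise but leaves the test at 0.05, and dilution works against a positive finding. The risk lies in the second look and in what the estimate would be taken to mean.

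Two further inferences are tempting. One is that a non-significant interaction blocks the 4-week contrast and costs power. The text makes the interaction a condition for the main effects only, and with two visits the interaction and the contrast are the same test. The other is that the interaction mixes in the 3-month visit. That is possible if the model includes that visit, but the article does not say that it does.

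**Conclusion.** The point holds as a should-fix matter of wording. The plan states a follow-up test that is unsuitable as evidence of a treatment effect and leaves its standing open.

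If a main effect after a null interaction is read as an intervention effect, the false-positive chance is about 0.0975 in place of 0.05. If the named contrast alone decides, it is 0.05. The 0.0975 rests on normality, equal variances and a common correlation. The dilution to 1.0 or 1.33 points rests on a constant 2-point effect after baseline. The imbalance figures also depend on the assumed correlation. The choice of primary contrast, its timing and the sample size are unaffected.

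**What to change.** In Statistical methods:

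1. State that the 1-df between-group contrast in change from baseline to 4 weeks alone decides the primary hypothesis, tested once at two-sided 0.05 whatever any omnibus interaction shows.
2. Delete the step to group and time main effects, or label it descriptive and not evidence of a treatment effect.
3. Apply the same rule to the secondary outcomes, with the corresponding between-group contrasts in change.

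The cost is about two sentences of wording, with no new data and no change in sample size. Follow-up is reported as complete, so the clarification should be recorded and dated before the unblinded comparison is run. If that comparison has already been run, the report should say so and present any main effect as descriptive.

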The SPPB score is based on timed measures of standing balance, walking speed and ability to rise from a chair. Each test is scored on a scale of 0 to 4 points, with a summary performance score range of 0–12 points using cut-point criteria established by Guralnik et al. [27]. A 0 score indicates poor function, whilst 12 indicates excellent function. If the participant is unable to perform a specific test, a score of 0 will be assigned. A score of 10 or lower is considered the cut-point for mobility impairment [27]. The SPPB was selected because it assesses overall functional performance that reflects physical function required to perform everyday tasks. It is hypothesised that the intervention will impact overall functional performance because this is the primary concern of most patients at medium- to long-term follow-up (6 weeks to 12 months) [26, 30]. The test has established validity and reliability in measuring physical performance in the elderly [27, 31, 32] with an intra-class correlation coefficient (ICC) equal to 0.82 [32], and it is a strong predictor of disability in non-disabled older persons [33]. The minimal detectable change values range from 0.54 [34] to 2 points [35], which suggests that a change in physical performance of 1 to 2 points is a clinically meaningful change in an older [34] and in-patient stable cardiovascular population [35]. Therefore, in the absence of data for cardiac surgery populations, the minimal important difference (MID) for this study was derived from prior research with a cohort of patients with stable cardiovascular conditions of 2 points, which is representative of our participant population. The SPPB has been shown to be reliable, valid and sensitive to change [36]. ICCs ranged from 0.88 to 0.92 for measures done 1 week apart, with a 6-month average ICC of 0.78 [36].

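### The primary SPPB analysis may be replaced by a dichotomised or transformed version; dichotomising would take power well below 0.80, and either route leaves the 2-point scale on which the trial was sized

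*Protocol article*

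**What the plan says.** Under Statistical methods, the protocol article defines the primary outcome as the change in SPPB from baseline to 4 weeks. It is tested by a contrast in a mixed repeated-measures analysis of variance. The section then adds: "If there are issues with non-normality or ceiling/floor effects of the SPPB, transformation or dichotomisation will be considered".

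Three other places bear on that sentence.

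- **Sample size.** The trial was sized "using the MID between the treated group of 2 points of a total possible score of 12 points", "with an SD of 2.7 points", and the section concludes that "29 participants are required per group (58 in total), based on a two-sample" *t* test.
- **Reporting.** At the end of Statistical methods, for all tests, *p* below 0.05 ("two-tailed) will be considered statistically significant, and mean differences (95% confidence intervals) will be reported").
- **Cut-point.** The only SPPB threshold in the document is in the description of the primary outcome: "A score of 10 or lower is considered the cut-point for mobility impairment". It classifies a score at one time point. Nothing links it to the analysis, whose outcome is a change.

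**The concern.** The sentence names two replacements for the form of the primary outcome and does not keep the score in points as the primary analysis. This is a choice that the article states, not a detail it leaves out, and it conflicts with the rest of the plan in three ways.

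- A dichotomised SPPB estimates a difference in proportions and would need a different model from the one named. It cannot be read against 2 points and cannot yield the promised mean difference.
- A transformed SPPB gives a mean difference, but not in points.
- Dichotomising a 13-level score discards information in a trial with 29 evaluable patients per arm and little power to spare.

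The choice also rests on looking at the trial data. Trial status says that all follow-up is complete. Blinding lists patients, outcome assessors and data management but does not mention the biostatistician who runs the analysis. At stake are the power of the single primary test, the meaning of its estimate, and confidence that the form of the outcome was not picked by result.

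**Working it through.** **Inputs from the document.** Difference 2 points, SD 2.7, two-sided type I error 0.05, power 0.80, 1:1 allocation, 29 per group, 72 after allowing for 20% dropout, score range 0 to 12, and a cut at 10 or lower versus above 10.

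**Assumptions.** The document gives no control-group SPPB mean at 4 weeks, so a range is shown. The SD of 2.7 is applied to the 4-week score on an underlying normal scale. The planned contrast is approximated by the two-sample *t* test on which the plan itself was sized.

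**1. The plan's own figure.** n per group = 2 × [2.7 × (1.960 + 0.842) / 2]² = 28.6, rounded up to 29. This reproduces. Power with 29 per group is 0.805 by the normal formula and 0.79 by the exact *t* test. For dropout, 58 / 0.80 = 72.5, against the stated 72, which is close enough.

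**2. Power if split at above 10.** A rounded score above 10 corresponds to 10.5 on the underlying scale. With control mean m:

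- p₁ = 1 − Φ[(10.5 − m) / 2.7] and p₂ = 1 − Φ[(10.5 − m − 2) / 2.7]
- power = Φ{ [(p₂ − p₁)√n − 1.960 √(2p̄(1 − p̄))] / √(p₁(1 − p₁) + p₂(1 − p₂)) }

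For m = 9: p₁ = 0.289, p₂ = 0.573, p̄ = 0.431. The numerator is 0.284 × 5.385 − 1.960 × 0.700 = 0.157 and the denominator is 0.671. Power = Φ(0.23) = 0.59.

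| Control mean | p₁ | p₂ | Power, 29 per arm | n per arm for 0.80 |
|---|---|---|---|---|
| 6 | 0.048 | 0.177 | 0.34 | 93 |
| 7 | 0.097 | 0.289 | 0.46 | 66 |
| 8 | 0.177 | 0.427 | 0.55 | 53 |
| 9 | 0.289 | 0.573 | 0.59 | 47 |
| 9.5 | 0.356 | 0.644 | 0.60 | 46 |
| 10 | 0.427 | 0.711 | 0.59 | 47 |
| 10.5 | 0.500 | 0.771 | 0.58 | 49 |

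The row for 9.5 is the best case, with the cut midway between the group means. Even there, 36 per arm with no dropout gives 0.70.

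**3. Like-for-like comparison on the bounded score.** Simulated trials (100,000 per setting, 29 per arm, scores rounded and clipped to 0 to 12, true shift 2 points) give:

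| Control mean | Score in points | Log-reflected transformation | Split at above 10 |
|---|---|---|---|
| 7 | 0.78 | 0.75 | 0.46 |
| 8 | 0.77 | 0.75 | 0.54 |
| 9 | 0.74 | 0.74 | 0.59 |
| 10 | 0.71 | 0.72 | 0.59 |

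The bound alone takes power a little below 0.80. Dichotomising removes a further 0.12 to 0.32. Transformation loses at most about 0.03 and gains about 0.01 at a mean of 10.

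**4. Type I error, same simulation with no true difference, means 7 to 10.**

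- Score in points alone: 0.049 to 0.050.
- Better of points and dichotomised: 0.075 to 0.092.
- Best of points, transformed and dichotomised: 0.081 to 0.098.
- As the last, with the cut also free among 7, 8, 9 and 10: 0.14 to 0.15.
- Switch decided only by the pooled distribution (illustrative trigger: more than 15% of all scores at 12) with the cut fixed at above 10: 0.046 to 0.050.

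**The case against.** The strongest reply is that the trigger is the shape of the distribution, not the treatment result. On that reading the clause does no harm to type I error, and the simulation confirms it: a rule applied to pooled scores with a fixed cut holds about 0.05. A reader might infer that the sentence itself inflates type I error. The document does not support that, because it nowhere plans to run several versions and keep the best. What remains is narrower. The text does not exclude a choice made with group results in view, so the error rate is left open.

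A reader might also infer that both fallbacks lose power. That holds for dichotomisation only. The objection to transformation is the loss of the scale in points.

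Nor can one say that the fallback is sure to be used. A bounded score in adults of 18 and over makes some ceiling effect plausible, but the document gives no SPPB mean or ceiling proportion for these patients, and the wording is only that the options will be considered.

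Finally, the exact trigger and cut may sit in an analysis plan that is not shown, and their absence from an article is not a fault. That reply stands for those details. It does not answer the article's own naming of dichotomisation as a remedy for the primary outcome, against its own sample size and reporting statement.

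**Conclusion.** The point holds in limited form. The article allows the primary SPPB analysis to be replaced by one that does not estimate the 2-point mean difference the trial was built on. If that replacement is a split at above 10, power with 29 per arm is about 0.54 to 0.59 for control means of 8 to 10, against 0.71 to 0.77 for the bounded score in points. Between 46 and 93 per arm would be needed to restore 0.80 over means of 6 to 10.5. Transformation is close to neutral for power and loses only the scale. Type I error is exposed, not shown to be inflated: up to about 0.10 with a fixed cut if the choice follows the results, and about 0.05 if it is made blind on pooled data. The sizes rest on the assumed control means, on an SD of 2.7 at 4 weeks, and on the *t* test as a stand-in for the planned contrast. The stated sample size of 29 per group is not in question.

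**What to change.** Replace the sentence with one that fixes the primary analysis whatever the distribution: the between-group difference in mean SPPB (0 to 12) at 4 weeks, adjusted for baseline SPPB, with its 95% confidence interval. If residuals are clearly non-normal, take the interval and *p* value from a bootstrap or permutation procedure, so that the estimate stays in points.

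Make a proportional-odds analysis of the 0 to 12 score the sensitivity analysis for ceiling effects. Any transformed version is likewise a sensitivity analysis, and the proportion above 10 is descriptive. Specify all of these before unblinding.

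In simulation on the same bounded score (29 per arm, control means 8 to 10), the baseline-adjusted comparison held type I error near 0.05. It had power of about 0.79 to 0.98 for assumed baseline to 4-week correlations of 0.5 to 0.78. That gain comes from the adjustment and depends on a correlation that the document does not give, so it is no measure of the harm done by the current sentence. If the sponsor prefers to keep the change contrast, retaining it in points as primary would also remove the problem described here.

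The cost is wording and one extra sensitivity model, with no new data and no change to the sample size.

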## Background

Cardiac surgery via a median sternotomy has been performed in over 1 million cases worldwide [1, 2] because it provides the best clinical outcome for patients with multiple-vessel disease and co-morbidities [3–7]. Despite these advantages, the incidence of sternal complications has remained relatively unchanged for the last 2 decades and is reported to be between 0.4% and 8% worldwide [8–11]. Sternal complications include dehiscence, wound infection, sternal instability/non-union and mediastinitis [11]. These complications are associated with significant morbidity and prolonged hospital length of stay, and they contribute to increased health care costs [8, 11, 12].

To prevent sternal complications, the routine implementation of sternal precautions that place restrictions on the use of the upper limbs and trunk commences immediately post-operatively. These precautions are used worldwide, although they are applied for variable periods of time (4 weeks to 3 months) post-operatively [8, 13, 14]. The evidence to support sternal precautions is limited to cadaver and replica bone model studies [15, 16]. In a foundational study, McGregor et al. found that a force of 220 ± 40 N was required to attain 2-mm distraction between sternal edges in the lateral direction, 263 ± 74 N in the anteroposterior direction and 325 ± 30 N in the rostrocaudal direction [16]. This prompted a recommendation to discourage the bilateral use of the upper limbs because this was thought to increase the distractive forces at the sternal edges [16]. From the outset, health care professionals, including surgeons, nurses and physiotherapists, routinely reinforce sternal precautions in their clinical practice. However, a recent study demonstrated that upper limb and trunk tasks cause only minimal micromotion of the sternal edges (<2 mm) as measured by real-time ultrasound, and this was the case for all tasks, including bilateral and unilateral arm elevation [17]. On the basis of these findings, restricting the use of the upper limbs and trunk in an attempt to prevent excessive sternal motion may be overly cautious. Sternal precautions in the form of physical restrictions may delay recovery, prolong return to function and delay hospital discharge, and as such may be overly restrictive [8, 18, 19].

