Pre-, intra- and post-operative variables • Date of cardiac surgery • Clinical information (left ventricular function, Canadian Cardiovascular Society functional classification, co-morbidities, graft type) • Type of cardiac surgery (including whether it was an emergency or elective procedure) • Other intra-operative details (including method of sternal closure, cardiopulmonary bypass time, operation time, adverse events) • Date of admission to and discharge from intensive care unit post-operatively • Risk factors for pre-, intra- and post-operative (i.e., duration of mechanical ventilation) • Type and use of pain medication (pre- and post-operatively) • Type and use of other medications (pre- and post-operatively) • Date of admission to and discharge from acute physiotherapy services • Details of physiotherapy treatment (including exercises and education provided) • Other adverse events during hospital admission (pre- and post-operatively leading to increase in length of stay); this includes superficial sternal infection, deep sternal infection, re-wiring, re-operation, pneumonia as defined in the Australian Society of Cardiac and Thoracic Surgeons (ASCTS) data • Date of readmission

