Previous studies have shown that unsupported, frequent coughing is the single main cause of mechanical stress through the sternum and may be a far more significant factor in the development of sternal complications [17, 19]. Further, recent evidence demonstrated that upper limbs and trunk movement cause minimal micromotion of the sternal edges (<2 mm) as measured by real-time ultrasound [17]. Therefore, it was proposed that strict post-operative movement restrictions may not be necessary for all patients [8, 13]. However, upper limb movements are part of post-operative standard physiotherapy treatment. In some institutions, this represents instructions on ‘no use of the arms’, or limiting the use of the arms to 90-degree elevation for varying periods of time [8, 13, 14, 25]. Concurrently, patients are encouraged to perform active movements of the upper limbs as part of their post-operative care following cardiac surgery with the aim of restoring physical function [8]. This creates a clinical dilemma collectively for both health professionals and patients [8, 13]. On the basis of findings of a recent survey conducted in Australia [13], we have chosen to modify sternal precaution guidelines encouraging the use of bilateral upper limbs and trunk activities with pain and discomfort as a safety guide in the intervention group to optimise sternal healing and functional recovery in this patient population. Specifically, participants will be allowed to resume their normal load-bearing activities at their own pace within pain-free limits by keeping their upper arms close to their body for common activities (e.g., getting out of bed, lifting and transferring). We hypothesise that this intervention will be safe and cause no harm to the participants. In addition, prior research suggests that unloaded movements within a pain-free range and loaded activity with the upper arms close to the body will not cause excessive stress on the sternal surgical site or bone [8, 19, 62, 65].

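### With about 0.3 to 6 sternal complications expected in 72 patients, the exploratory logistic regression cannot identify risk factors reliably

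*Protocol article*

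**What the plan says.** The third secondary aim, under Trial objective and hypothesis, is to explore which patient and peri-operative factors go with complications after sternotomy. The Statistical methods section gives the method: "Logistic regression will be used to determine pre-, peri- and post-operative risk factors associated with the development of post-sternotomy complications". The next sentence calls the analysis exploratory and says it may show trends in predictors already published. Six are given as examples: sex, diabetes, obesity, use of both mammary arteries, re-operation and transfusion. The same paragraph ends by setting a two-tailed p<0.05 for all tests, with no exemption for this analysis.

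The Background says the incidence of sternal complications "is reported to be between 0.4% and 8% worldwide" and describes them: "Sternal complications include dehiscence, wound infection, sternal instability/non-union and mediastinitis". Table 2, under Data collection, separately records adverse events during admission; "this includes superficial sternal infection, deep sternal infection, re-wiring, re-operation, pneumonia".

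The sample size was set for the Short Physical Performance Battery alone: "it is anticipated that 29 participants are required per group (58 in total), based on a two-sample *t* test". "This sample was increased to 72 participants on the basis of a predicted 20% dropout rate". No event count is given for the regression.

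**The concern.** Logistic regression draws its information from the number of events, not the number of patients. A trial sized for a difference in a continuous score may contain almost no events of an uncommon complication. Three things can then go wrong. There may be nothing to model. A predictor may be wholly absent from the cases, or from the non-exposed side of the events, so that its maximum-likelihood odds ratio is zero or infinite. Or a model may fit but have so little power that a non-significant result says nothing and a significant one is likely to be exaggerated.

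At stake is a secondary, exploratory aim. No primary or key secondary conclusion depends on it. But odds ratios judged at p<0.05 would be published as risk factors, or non-factors, for sternal complications on the strength of a handful of cases.

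**Working it through.** **Inputs from the document.** Incidence 0.4% to 8% (Background); 72 patients, 58 before the dropout allowance (Sample size); six example predictors and the p<0.05 rule (Statistical methods). The 4% row in the table is an intermediate value chosen for illustration.

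**The plan's own figure.** For a difference of 2 and SD 2.7, two-sided 0.05 and power 0.80, the normal approximation gives n = 2(1.96 + 0.84)² × 2.7²/2² = 28.6, so 29 per group, as stated. Then 58/0.80 = 72.5, against 72 stated. The sample size is reproduced closely enough, and it concerns only the primary outcome.

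**Expected events.** 72 × 0.004 = 0.29 and 72 × 0.08 = 5.76. With 58 completers: 58 × 0.004 = 0.23 and 58 × 0.08 = 4.64.

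**Spread of the count (binomial, 72 patients).** The chance of no event is 0.996^72 = 0.75 at 0.4%, 0.96^72 = 0.05 at 4% and 0.92^72 = 0.002 at 8%. The chance of ten or more at 8% is 0.06.

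**Six predictors jointly.** Events per predictor: 0.29/6 = 0.05 to 5.76/6 = 0.96. Under the common working rule of ten events per predictor (an assumption, not in the document), six predictors need 60 events: 60/0.08 = 750 patients, or 60/0.004 = 15,000.

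How often the joint model fails to fit depends on exposure prevalences that the document does not give. With six events, an exposure of prevalence q is absent from every case with probability (1 − q)^6: 0.12 at 30%, 0.53 at 10% and 0.74 at 5%. In a simulation of 400 runs with assumed prevalences of 5% to 35% and each odds ratio 2, there was no finite maximum-likelihood fit in about 80% of runs at 8% incidence and 95% at 4%. These two percentages are illustrative only.

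**One predictor at a time.** Assume 22 of 72 patients exposed (about 30%) and a true odds ratio of 3. The risks p0 (unexposed) and p1 (exposed) are solved so that the overall incidence matches. No finite estimate exists when either group has no events, so its probability is close to 1 − [1 − (1 − p1)^22][1 − (1 − p0)^50]. Power is for Fisher's exact test at 0.05, summed over all possible 2×2 tables.

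| Incidence | p0, p1 | No finite estimate | Fisher power |
|---|---|---|---|
| 8% | 5.3%, 14.3% | 1 − 0.967 × 0.934 = 0.10 | 0.19 |
| 4% | 2.6%, 7.3% | 1 − 0.813 × 0.728 = 0.41 | 0.09 |
| 0.4% | 0.25%, 0.75% | 1 − 0.152 × 0.118 = 0.98 | 0.001 |

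The Wald test, when a finite estimate exists, does no better: 0.16, 0.03 and below 0.001. A true odds ratio of 5 at 8% incidence raises Fisher power only to 0.38.

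**The case against.** The strongest defence is that the plan claims little. Both the aims and the Statistical methods section call the analysis exploratory and speak of trends, and nothing else depends on it. The verb *determine* should be read with that limit. This stands, and it lowers the importance of the point. It does not make an odds ratio estimable from one or two events, and the p<0.05 rule still applies.

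Second, the text speaks of predictors having an individual effect, which allows one-predictor models. At 8% incidence such a model can be fitted in about 90% of trials. So it would be wrong to say that the regression must fail. At the top of the range the trouble is low power; lower down it is also non-estimability.

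Three stronger readings are tempting, and the document does not support them.

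- A reader might infer that re-operation serves as both predictor and outcome. The Background's description of sternal complications does not include it. Table 2 lists it as an adverse event during admission, next to pneumonia, and never calls that list the regression outcome. In Statistical methods it appears as a published predictor of sternal infection. Overlap is possible because the outcome is not tied to either list, but it is not stated.
- A reader might infer that the randomised arm is deliberately left out. The six factors are literature examples, where this trial's arm could not appear, and a full covariate list may sit in an analysis plan that is not shown.
- A reader might set the Discussion's statement "We hypothesise that this intervention will be safe and cause no harm to the participants" beside this and conclude that safety goes unexamined or will be wrongly claimed. That is a hypothesis in the Discussion and no test is attached to it. The article plans descriptive counts, lists a sternal instability scale among its outcomes and provides for committee review of serious adverse events.

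**Conclusion.** The point holds in this form: on the document's own incidence and sample size, about 0.3 to 6 events are expected, too few for the planned logistic regression to identify risk factors reliably. The event counts, and the ceiling of about one event per predictor for a joint model of six, need no assumption beyond the document's figures and independent patients. The one-predictor results (power of 19% at best for an odds ratio of 3; no finite estimate in 10% to 98% of trials) rest on the assumed 30% prevalence and odds ratio. The simulated joint-model failure rates rest on assumed prevalences, and the conclusion does not depend on them. The finding is confined to an exploratory aim and leaves the primary analysis untouched. The place of re-operation is a matter for clarification, not an established error.

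**What to change.** Replace the sentence on logistic regression with three statements.

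1. Sternal complications are reported as counts and percentages by arm, with exact 95% confidence intervals.
2. Any predictors are shown one at a time, with Firth or exact estimates and confidence intervals, as description only and outside the p<0.05 rule. If no event occurs, no model is fitted.
3. The outcome is defined, for example by the Background's description of sternal complications, so that re-operation is neither a component nor a consequence of it. If that cannot be separated, re-operation is not used as a predictor.

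The counts should be read with their limits in view: zero events among 36 patients in an arm would still leave a two-sided 95% upper limit of 1 − 0.025^(1/36) = 9.7%, above the whole 0.4% to 8% range.

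The cost is a change of analysis wording. The article reports follow-up as complete, and no new data are needed. The downside is the loss of a formal risk-factor analysis that could not have been informative at this size.
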